## STUDY POPULATION

A total of 32 pediatric subjects with SBS, aged 2 years – 18 years and PN dependent are expected to be enrolled in this open labeled study. Eligibility will be established by the investigator based on the inclusion and exclusion criteria.

### Inclusion Criteria

To be considered eligible to participate in this study, a subject must meet all the inclusion criteria listed below:

1. Male or female patients, aged 2 years – 18 years, inclusively.
2. Diagnosed with SBS, as determined by medical history and PN dependence (i.e. need for PN for >60 days after intestinal resection or a bowel length <25% of expected).
3. Congenital or acquired gastrointestinal disease requiring surgical intervention that has occurred at least 3 months prior to screening.
4. Patient is on parenteral lipid and at least 30% of daily caloric and fluid intake has been provided by PN for at least 6 months prior to screening.
5. Stable PN nutrition requirement, determined by less than 5% reduction in PN nutrition for at least 1 month prior to screening, or at the discretion of the investigator.
6. The patient has a Central Venous Catheter (CVC) at the time of study inclusion.
7. Screening direct bilirubin that is in the normal range for age or is not determined to be clinically significant by the investigator.
8. The patient has an existing feeding tube, receiving enteral nutrition via an enteral feeding pump at a rate>10ml/hr but <120ml/hr, and is able to tolerate at least 10 ml/kg/day enteral nutrition with which the RELiZORB cartridge can be used.
9. Stable enteral nutrition requirement with no change in formula composition or rate for at least 1 month prior to screening.
10. The patient or a parent or legal guardian of the patient is able to read, understand, and is willing to provide informed consent (or assent, if applicable) for the patient.
11. The patient (if assent is applicable) or a parent or legal guardian is able to understand the requirements of the study and is willing to bring the patient to all clinic visits and complete all study related procedures (as determined by the investigator).
12. A parent or legal guardian is willing to provide written authorization for the use and disclosure of protected health information.

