| **Inclusion criteria:**   1. Male or female patients, ages 2 years to 18 years, inclusive. 2. Diagnosed with SBS, as determined by medical history and PN dependence (i.e. need for PN for >60 days after intestinal resection or a bowel length <25% of expected). 3. Congenital or acquired gastrointestinal disease requiring surgical intervention that has occurred at least 3 months prior to screening. 4. Patient is on parenteral lipid and at least 30% of daily caloric and fluid intake has been provided by PN for a least 6 months prior to screening 5. Stable PN nutrition requirement, determined by less than 5% reduction in PN nutrition calories for at least 1 month prior to screening, or at the discretion of the investigator. 6. Screening direct bilirubin that is in the normal range for age and is not determined to be clinically significant by the investigator. 7. Subject has an existing feeding tube, is receiving enteral nutrition via a pump at a rate>10ml/hr but <120ml/hr, and is able to tolerate at least 10 ml/kg/day enteral nutrition. 8. Stable enteral nutrition requirement with no change in formula composition or rate for at least 1 month prior to screening. 9. The parent or legal guardian of the patient is able to read, understand, and is willing to provide informed consent (and assent, if applicable). 10. The patient (if assent is applicable) or parent or legal guardian of the patient is able to understand the requirements of the study and is willing to bring the patient to all clinic visits and complete all study related procedures (as determined by the investigator). 11. A parent or legal guardian is willing to provide written authorization for the use and disclosure of protected health information. | |

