# STUDY DESIGN

## BASIC DESIGN CHARACTERISTICS

This study is a phase 3, open labeled uncontrolled single center,
clinical trial to determine the safety, tolerability, and bioavailability of the RELiZORB enzyme cartridge with enteral nutrition when used daily for a total 90 days of treatment when given to pediatric subjects with SBS, aged 2 years – 18 years, who have been PN dependent for at least 6 months.

Subjects with a signed informed consent will be enrolled in the study. Results from screening must not show any clinically significant abnormalities in order for the subject to progress to the enrollment and treatment phases of the trial. During the screening visit, subjects and legal guardians will also receive education from a registered dietician on recording caloric intake and composition in oral and enteral feeds, and PN. As part of this education, the subject and parent/guardian will receive access to a nutrition/food tracking phone application (Cronometer) to assist them with this task throughout the study. If there is no electronic capability, a paper diary will be provided. The subject and parent/guardian will also receive education from a registered nurse on accurate and complete stool collection. Subjects will be provided with a standardized weight scale for at-home weight recording.

Upon completing screening and enrollment, subjects and their legal guardians will be instructed to record total calories and composition in oral and enteral feeds and TPN and to collect all stool for 72 hours (Days -3 to -1) prior to the first day of treatment. The stool collection and recording will be repeated in the 72-hours preceding the final study visit (Days 87-89). All stool will be collected in a single container and kept refrigerated during collection. If necessary (for example, out of state participants, excessively watery stools), subjects will be admitted to our dedicated research center during this collection period.

On the first day of treatment (Day 1), all subjects will use the RELiZORB enzyme cartridge to administer their enteral nutrition and will continue to use a cartridge daily for a total of 90 days. The study device will be used with enteral nutrition administered to the subject daily by a parent or guardian for 90 days (Day 1 to Day 90).

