### Sample Size

Historical review of patients followed by the Center for Advanced Intestinal Failure (CAIR) at Boston Children’s Hospital suggests that an average of 8 patients per year can be expected to meet the eligibility criteria, for a total of 32 subjects over 48 months. Additionally, patients currently followed by CAIR who are eligible and consent to the study will be enrolled, thus providing additional protection against attrition. Precision-based power calculations were determined with nQuery Advisor 7.0.

The primary outcome is the change in PN calories from baseline, assessed weekly at 13 assessments (study days 7, 14, 21, 28, 35, 42, 49, 56, 63, 70, 77, 84, and 90) using a baseline-adjusted time-weighted average (AUC_7-90_). It is believed that even a 10% reduction in PN calories would be clinically meaningful. In adults receiving teduglutide intended to improve enteral absorption in PN dependent patients with intestinal failure, a similar aim of 20% reduction was used to assess efficacy^24^. When this adult protocol was refined for a pediatric population, it was felt at least a 10% reduction in the volume of PN/IV support from baseline after 12 weeks of treatment was a reliable pharmacodynamic marker of increased intestinal absorptive capacity in pediatric short bowel syndrome patients who were dependent on PN/IV support. Although a 20% reduction from baseline in volume of PN/IV was used as the primary endpoint in the adult study, when adapted for a pediatric population, a ≥10% reduction was considered a valid pharmacodynamics (PD) marker of increased intestinal absorptive capacity, as agreed to by the expert clinicians with whom that study’s sponsors consulted (NPS Pharmaceuticals, Inc.). Based on the design of the teduglutide studies it was felt that the data provide similar support for a ≥10% reduction at Day 90 as a predictor of pharmacodynamic effect with the use of the RELiZORB device.

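### The PN stability criterion limits only reductions, so a child whose PN was recently raised can enter as stable; if that rise is later undone, the fall counts as reduction on the primary endpoint

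*Protocol*

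**What the plan says.** Protocol section 3.2.1, criterion 5, defines stability as "Stable PN nutrition requirement, determined by less than 5% reduction in PN nutrition for at least 1 month prior to screening" and adds the alternative "or at the discretion of the investigator". The synopsis has the same one-sided rule, specified in calories: "determined by less than 5% reduction in PN nutrition calories for at least 1 month prior to screening".

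The neighbouring criteria do not cover an increase in PN. Criterion 4 is a floor: "at least 30% of daily caloric and fluid intake has been provided by PN for at least 6 months prior to screening". Criterion 9 is two-sided but concerns tube feeding only: "Stable enteral nutrition requirement with no change in formula composition or rate for at least 1 month prior to screening".

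Section 3.1 describes the design: "This study is a phase 3, open labeled uncontrolled single center". Section 10.2.2 divides each PN value by the single Day 1 value and takes a time-weighted average over Days 7 to 90, with 1 meaning no change. Section 10.2.5 sets the target: "It is believed that even a 10% reduction in PN calories would be clinically meaningful".

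**The concern.** A stability rule should ensure that the baseline represents the child's usual PN. This one excludes children already being weaned, which is the more obvious bias, but leaves the opposite case open. A child whose PN was raised by a fifth two weeks before screening shows no reduction and qualifies. The protocol itself foresees increases: its standard-of-care section (7.1.5) raises PN when oral energy intake falls below resting needs for more than 3 days, and that need not involve any change in tube feeding.

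If the Day 1 value is temporarily high, a return to usual PN lowers every later ratio without any device effect. With no concurrent control, the primary result absorbs that fall. The covariates listed in section 10.2.4 do not include the PN trend before entry, and the per-protocol exclusions do not mention it. A child who meets criterion 5 as written is not a protocol deviation on this account.

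**Working it through.** **The plan's own figures (section 10.2.5).** Inputs: n = 32, SD 0.14 or 0.28, observed mean 0.80. The interval is 0.80 ± t(0.975, 31) × SD/√32.
- SD 0.14: 0.750 to 0.850, half-width 0.05. The protocol's interval is reproduced.
- SD 0.28: 0.699 to 0.901. The protocol's rounded (0.7, 0.9) is reproduced.
- Power at effect size 0.51, two-sided 0.05: 79.8%, against the stated 80%.

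These figures stand. The issue is what the mean estimates.

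**Effect on one child, zero device effect (illustration).** Let PN be raised by a fraction x before Day 1 and later return fully to its earlier level. The ratio then settles at 1/(1+x). AUC7-90 uses the protocol's trapezoid formula on its 13 assessment days, a span of 83 days.

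Step return (ratio 1 through Day 21, then 1/(1+x) from Day 28), with x = 0.20:
- Days 7 to 21: 14 × 1 = 14.00
- Days 21 to 28: 7 × (1 + 0.8333)/2 = 6.42
- Days 28 to 90: 62 × 0.8333 = 51.67
- AUC7-90 = 72.08/83 = 0.87

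The same step return gives 0.93 for x = 0.10 and 0.84 for x = 0.25.

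Linear return from Day 1:

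| Rise before Day 1 | Final ratio | AUC7-90, back by Day 28 | AUC7-90, back by Day 90 |
|---|---|---|---|
| 10% | 0.909 | 0.918 | 0.951 |
| 20% | 0.833 | 0.850 | 0.911 |
| 30% | 0.769 | 0.792 | 0.877 |

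**Effect on the trial mean.** Shift = share affected × (1 − AUC7-90). For a 20% rise:

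| Share affected | Step return, Day 28 | Linear return, Day 28 | Linear return, Day 90 |
|---|---|---|---|
| 10% | 0.10 × 0.1315 = 0.013 | 0.015 | 0.009 |
| 25% | 0.25 × 0.1315 = 0.033 | 0.038 | 0.022 |

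The shares, the size of the rise and the speed of return are assumptions; the protocol gives none of them. The shifts are below the 0.10 target. At a 25% share with return by Day 28 they approach the 0.05 half-width at SD 0.14. In the protocol's conservative case (SD 0.28) the upper limit already sits at about 0.90, so a shift of one or two hundredths could decide whether a reduction smaller than 10% is excluded.

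**What a two-sided bound leaves.** A rise just under 5%, fully undone, gives at most 1 − 1/1.05 = 0.048 for that child.

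**The case against.** Several points on the other side stand.

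- **Direction.** A reader might infer that a recent rise can only push AUC7-90 below 1. That holds only if the rise is undone. Section 5.0 ties PN changes to keeping the child on the growth trend, and section 7.1.5 raises PN when oral intake falls. A rise that persists gives a ratio near 1, and one that continues gives a ratio above 1. The net sign in a mixed group is not fixed by the document.
- **Other entry controls.** The criterion is headed as a stable requirement. Screening must show no clinically significant abnormality, and exclusion 14 lets the investigator refuse an unsuitable child. Illness that changed the tube-feed rate in the month before screening would fail criterion 9. These controls probably shrink the affected group, but none requires rejecting a child because PN was raised. The discretion clause can also waive the 5% limit itself.
- **Size.** Shifts near the 10% target need large rises in a large share of children. At shares of 10 to 25% and a 20% rise, the shift is a few percent at most.
- **Analysis.** A reader might infer that no analysis could deal with this. The protocol text does not support that. PN history for the month before screening is needed to judge criterion 5, so a sensitivity analysis is feasible, and a statistical analysis plan that is not shown may contain one.

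**Conclusion.** The wording gap is real. Criterion 5 bounds reductions only, and no other criterion bars a recent PN increase. In an uncontrolled trial that divides by a single Day 1 value, reversal of a temporary rise is scored as reduction.

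The impact is uncertain because the protocol gives no frequency, size or reversibility of such rises. Assuming a 20% rise fully undone by Day 28 and no device effect, the individual AUC7-90 is about 0.85 to 0.87. The mean shift is then about 1.5% with 10% of children affected and 3 to 4% with 25%; slower return gives less. It would be tempting to conclude that the primary result is invalid or that an observed 10% reduction could be wholly artefact. At these shares the figures do not support that. This is a should-fix eligibility improvement, not a defect that must be repaired before the trial can proceed.

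**What to change.** 1. In the synopsis and in section 3.2.1, make the bound two-sided with the protocol's own 5%: PN calories to have changed by less than 5%, up or down, over at least the month before screening. Name calories in both places.
2. State that investigator discretion may not be used to admit a child with a recent PN increase, or require each such use to be recorded with its reason. Without this, the two-sided bound can be bypassed.
3. For all enrolled children, tabulate the change in PN calories over the month before screening. Repeat the primary analysis without those whose PN rose by 5% or more or who entered by discretion.

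The cost is a short eligibility amendment and one sensitivity analysis. Some recently escalated children would enter about a month later, which matters somewhat with about 8 eligible patients expected per year. A residual artefact of up to about 4.8% per affected child remains possible, and the single Day 1 denominator is unchanged.

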### Exclusion Criteria

To be eligible for entry into the study, the subject must not meet any of the exclusion criteria listed below:

1. Other causes of chronic liver disease other than SBS (i.e. hepatitis C, cystic fibrosis, biliary atresia, alpha 1 anti-trypsin deficiency, and Alagille syndrome).
2. The patient has had a bowel lengthening procedure, including but not limited to, a STEP procedure.
3. Any serum triglyceride concentration >400 mg/dL at screening.
4. Pancreatic insufficiency as defined as the use of pancreatic enzymes within 30 days prior to screening.
5. Evidence of untreated intestinal obstruction or active stenosis, as determined by the investigator.
6. Unstable absorption due to cystic fibrosis or known DNA abnormalities (i.e., familial adenomatous polyposis, Fanconi syndrome) as determined by the investigator.
7. History of microvillus inclusion disease, as determined by medical history.
8. Severe known dysmotility syndrome (i.e., pseudo-obstruction, gastroschisis-related motility disorders), as determined by the investigator.
9. Initiation of teduglutide or other GLP-2 analogues within 6 months of screening
10. Use of growth hormone, or supplemental glutamine within 3 months prior to screening.
11. Use of cisapride within 30 days prior to screening.
12. Active clinically significant pancreatic or biliary disease, as determined by the investigator.
13. Receiving enteral nutrition via any formula that is not compatible with the RELiZORB cartridge (for example, insoluble fiber-containing formulas).
14. Determined by the investigator to be unsuitable for participation in this trial for any reason.

## ENDPOINTS

### Primary efficacy endpoint

The primary efficacy endpoint is the change in PN calories since baseline, assessed weekly throughout the study.

### Secondary efficacy endpoint

The secondary efficacy endpoint is the change in body weight (weight-for-age z-score) since baseline, assessed weekly throughout the study.

### Safety endpoints

The safety endpoints include:

- Subject incidence of adverse events, including changes in stool consistency assessed by Bristol scale, changes in stool amount/frequency (if applicable), increased ostomy output (if applicable, defined as >2.5 mL/kg/hour), the need to decrease enteral feeds, changes in urine color assessed by Dehydration Color scale, and discontinuation from the study treatment.
- Subject incidence of abnormalities in vital signs, assessed at baseline, Day 7, 14, 28, 60, and 90.
- Subject incidence of abnormalities in hematology and biochemistry parameters assessed at baseline, Day 7, 14, 28, 60, and 90.

### Exploratory endpoints

- Change in 72-hour fecal fat composition and coefficient of fat absorption from enrollment, assessed at Days -3 to -1, to Days 87-89.
- Change in plasma serum fatty acid profile, and fat-soluble vitamins (A, D, E, and K) from baseline, assessed at Day 7, 14, 28, 60, and 90.
- Change in height (height-for-age z-score) and head circumference (head-circumference-for-age z-score) [in subjects < 36 months]) from baseline, assessed at Day 7, 14, 28, 60, and 90.
- Change in BMI z-score from baseline, assessed at Day 7, 14, 28, 60 and 90.
- Change in PN volume from baseline, assessed weekly.
- Change in enteral nutrition tolerance (calories and volume) from baseline, assessed weekly.
- Change in oral nutrition tolerance (calories and volume) from baseline, assessed weekly.
- Ability to wean from PN, assessed over the entire course of the study.

## DROPOUTS

Subjects who are enrolled but do not receive the RELiZORB enzyme cartridge will be considered dropouts. Furthermore, enrolled subjects who receive the RELiZORB enzyme cartridge and do not complete any study assessments through Day 90 will be considered dropouts. Dropouts will be replaced in order to reach the goal of 32 subjects with evaluable data. Patients with at least one post-baseline study assessment will be retained for analysis.

**3.5** **STUDY VISIT COMPENSATION**

Subjects will be paid $100.00 compensation for each research visit that they complete, with compensation provided through a service called ClinCard. Each subject/family will also be provided with a parking voucher and food voucher for each visit or will be reimbursed through the use of the ClinCard at the end of each study visit for study-related expenses such as travel, parking and meals, and other study-related expenses if a receipt is provided.

Subjects/families traveling a radius greater than 50 miles from BCH will be compensated for their travel expenses. Patients and families will be reimbursed for roundtrip travel expenses (i.e., airfare, gasoline, parking) and hotel stays at the Inn at Longwood Medical (or up to $225.00 a night if subjects stay at another hotel). Excluding travel expenses (if necessary) this will add up to a total of $1,402.00 if the subject completes all the research visits. If the subject leaves the study early, or is withdrawn at the discretion of the study physician, the subject will only be paid for the visits he/she has completed.

This research study will use a service called ClinCard® by the company Greenphire, www.greenphire.com, to manage all payments associated with the subject’s participation in study visits, time and travel related to participation in the study. ClinCard/Greenphire will provide documentation for the subject’s taxes (1099 form) and to the hospital. Boston Children’s Hospital has contracted with ClinCard/Greenphire to provide this service but Boston Children’s Hospital and ClinCard/Greenphire are separate entities and have no other relationship. ClinCard/Greenphire is solely responsible for the security of any information provided to them.

At each visit, the subject will receive a parking voucher and $25 for meal expenses. This $25 will also be loaded onto the ClinCard at each visit. If the subject resides out of state, the travel expenses as described above will be covered. The subject will also be compensated for completing the study diaries. The subject will be reimbursed $5.00 per completed diary.

If subjects live outside a 50-mile radius of BCH and travel to their study visits by car, they will be reimbursed for their round trip. We will calculate the appropriate reimbursement based on the IRS standard mileage rate for the calendar year and add that amount to the subject’s ClinCard.

Compensation Break Down

| **Item** | **Cost per day** | **# of days** | **Total** |
| --- | --- | --- | --- |
| Patient Stipend | $100 | up to 7 | $700 |
| Diary Completion | $5 | up to 90 | $450 |
| Parking Voucher | $11 | up to 7 | $77 |
| Meal Voucher | $25 | up to 7 | $175 |
| Total | | | $1402 |

# STUDY DEVICE

## IDENTIFICATION AND DESCRIPTON OF INVESTIGATIONAL PRODUCT

All investigational products used in this study will be manufactured, tested, labeled, and released according to current legal requirements and Good Manufacturing Practice (GMP).

### Investigational Product

RELiZORB is a single-use, point-of-care digestive enzyme cartridge that connects in-line with existing enteral feeding pump tubing sets and patient extension sets or enteral feeding tubes. RELiZORB is designed to hydrolyze (digest) fats contained in enteral formulas, mimicking the function of the digestive enzyme lipase that is normally secreted by the pancreas, the body’s digestive organ. By hydrolyzing (digesting) fats from enteral formulas, RELiZORB allows for the delivery of absorbable fatty acids and monoglycerides to patients.

RELiZORB is comprised of a clear cylindrical, plastic cartridge with a single inlet connection port and a single purple outlet connection port. The inlet and outlet ports of RELiZORB are intended to connect in-line with enteral feeding pump tubing sets and patient extension sets or enteral feeding sets. Inside the cartridge, there are small white beads. The digestive enzyme, lipase, is covalently bound to the small white beads. The lipase-bead complex, iLipaseTM (immobilized lipase), is retained within the cartridge during use by filters on both ends of the cartridge. The fat in enteral formulas is hydrolyzed as it comes in contact with iLipase as the formula passes through the cartridge.

